#### Quantitative data collection

Quantitative data collection takes place at enrollment (12–24 weeks gestation) and at 6 and 12 months postpartum (Figure 3). Participants in both groups (i.e., cash + care and care only) complete the baseline survey prior to receiving the cash disbursement, financial counseling, or care services. Survey data is collected through REDCap, a secure, web-based application that complies with HIPAA regulations. All data collection procedures follow approaches used in other local studies. Each survey is administered via an interviewer over the phone. Each question is read to the participant; responses are recorded on a tablet with a secure internet connection. All data management standards reflect the goal of reproducible research. To reduce data entry errors and omissions, we take advantage of REDCap’s built-in quality control functions. Data integrity is aided by the system’s automated logging of all input and edits. After each survey is complete, CRs send the participant a gift card (electronically or by text) and a community resource guide. Participants receive $50 for completion of the baseline survey, and the amount is increased by $25 for each subsequent survey.

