Stress will be measured through two scales. First, perceived stress will be measured with the ten-item Perceived Stress Scale (PSS) (35). Scores range from 0–40 and will be categorized into three groups as low stress (0–13), moderate stress (14–26), and high stress (27–40). Second, parental stress will be measured using three modified subscales of The Parental Cognitions and Conduct Toward the Infant Scale (PACOTIS), including: parental self-efficacy (six items), perceived parental impact (five items), and parental overprotection (four items) (36). Items are scored from 0 to 10 with higher scores indicating higher levels of self-efficacy, parental impact, and overprotection. Mean scores for each subscale will be used for analysis. Ability to meet basic needs will be measured through three domains: financial, food, and housing insecurity. Financial insecurity will be measured using the 10-item Consumer Financial Protection Bureau Financial Wellbeing Scale (37). Continuous scores ranging from 0 to 20 will be categorized by quartiles for analysis (38). The validated, two question Hunger Vital Sign screener (39) will be used to measure households at risk of food insecurity, and housing insecurity will be assessed using up to 16 items on history of homelessness, history of eviction, and falling behind on rent and utilities. Engagement in health care will be captured using prenatal care attendance data from the birth certificates. Specifically, adequacy of prenatal care (APCNU) is assessed using the Kotelchuck index by creating a ratio of observed prenatal care visits to expected prenatal care visits, relative to the American College of Gynecology recommended standard of care, classified as inadequate, intermediate, adequate or adequate plus (40). Parent–child attachment will be assessed using the Maternal Postnatal Attachment measure, a validated continuous scale (41). The scale consists of 19 items which ask the birthing parent to reflect on their thoughts and feelings toward their baby (42).

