To assess the feasibility and acceptability of PJB, we will use routinely collected data on study engagement among potential participants and 12-month endline survey data among PJB participants. Quantitative data analysis: Feasibility: We will assess the number and proportion of participants reached by PJB by creating quarterly reports from the routine data. We will compile absolute numbers for the following: (1) # who indicate interest; (2) # invited to enroll; (3) # who enroll; (4) # who are referred for care services. Acceptability: We will describe perceived acceptability quantitatively using 11 items on spending and decision-making control and ten items about the timing of GI payments from the endline survey. Acceptability of each care service will be evaluated using six items from the endline survey and acceptability of PJB and its evaluation will be assessed using three survey items. Qualitative data analysis: We will also examine perceived acceptability in the participatory session and will analyze data following procedures in Aim 2.

###### Aim 2

Examine *whether* and *how* a guaranteed income affects parental stress, ability to meet basic needs, engagement in healthcare and bandwidth for parenting among recipients of the cash + care. Quantitative data analysis: we will use survey data to examine *whether* receiving cash + care affects outcomes using two steps. First, we will describe baseline demographic characteristics among those who receive cash + care. Second, we will examine differences in parental stress, basic needs, engagement in care and bandwidth for parenting over follow-up (baseline, 6 months postpartum, and 12 months postpartum surveys). We will use mixed effects regression models with a fixed effect for time (categorical) and random participant-level intercepts. We will examine the sensitivity of our findings to the inclusion of key potential confounders in the model, including SES and pregnancy-related variables (e.g., gravidity, parity, maternal health conditions). Using these models, we will estimate and report the average difference in outcome between groups over follow-up with 95% confidence intervals. We will also characterize outcome patterns over time by presenting estimated mean outcomes at each time point individually.

###### Aim 3

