Explore the preliminary impact of PJB on parental mental health and prematurity. The purpose of the PJB is to reduce disparities in birth outcomes. Given the limited numbers of participants in this pilot program and evaluation study, however, we are underpowered to examine such disparities. Consequently, birth outcomes are included as exploratory analysis for potential signals of GI impact. Another important outcome for the PJB evaluation study is perinatal depression, which we do have sufficient statistical power to examine. Perinatal depression is also associated with adverse birth outcomes and can be a marker for perinatal health.

To investigate post-baseline differences in continuous EPDS depression score in the cash + care and care groups, our primary analyses will use mixed effects regression models with fixed effects for time (baseline, 6 months postpartum and 12 months postpartum), group, and the interaction between time and group and random participant-level intercepts. Using these models, we will estimate and report the average difference in depression score between groups over follow-up with 95% confidence intervals. We will also characterize outcome patterns over time by presenting estimated mean outcomes at each time point individually. We will use the same approach to examine post-intervention differences anxiety score. In secondary analyses, we will examine differences in infant birthweight and preterm birth in the cash + care vs. care groups using logistic regression. Birthweight and gestational age at birth will be determined using data from birth records and classified as low birthweight <2,500 grams (y/n) and preterm birth <37 weeks (y/n). We will examine the sensitivity of our findings to the inclusion of key potential confounders in our models, including SES and pregnancy-related variables (e.g., gravidity, parity, maternal health conditions).

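### Aim 2's confounder check is run in a recipients-only, time-only model, where baseline covariates say nothing about whether the change is due to cash

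*Protocol article*

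**What the plan says.** All references are to the protocol article, Part 4.

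- **Quantitative data analysis, Aim 2, population.** The aim concerns effects on stress, basic needs, engagement in healthcare and "bandwidth for parenting among recipients of the cash + care" group. Its first analysis step describes the baseline characteristics of recipients only.
- **Aim 2, model.** "We will use mixed effects regression models with a fixed effect for time (categorical) and random participant-level intercepts". There is no group term and no time-by-group term.
- **Aim 2, confounder check.** "We will examine the sensitivity of our findings to the inclusion of key potential confounders in the model, including SES and pregnancy-related variables", with gravidity, parity and maternal health conditions as examples.
- **Aim 2, reported quantity.** "Using these models, we will estimate and report the average difference in outcome between groups over follow-up with 95% confidence intervals".
- **Aim 3.** The EPDS model has time, group and their interaction, plus the random intercept. It is followed by nearly the same check: "We will examine the sensitivity of our findings to the inclusion of key potential confounders in our models, including SES and pregnancy-related variables".
- **Quantitative data collection.** "Quantitative data collection takes place at enrollment (12–24 weeks gestation) and at 6 and 12 months postpartum". Both groups "complete the baseline survey prior to receiving the cash disbursement, financial counseling, or care services".

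**The concern.** One survey comes before both the cash and the birth; the other two come after both. In a model fitted to recipients with only a time effect, any effect of cash is therefore mixed with everything else that changes between mid-pregnancy and the first postpartum year. That is the main rival explanation of a change.

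The check named for Aim 2 does not address it. SES, gravidity, parity and health conditions at baseline differ between people, whereas the time effects compare each person with herself. The result will look stable whether the cash did everything or nothing, and a reader could take that stability as support for a causal answer to Aim 2's *whether* question.

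The same paragraph then promises a difference between groups, which a model without a group term cannot produce. The Aim 3 text shows how the plan writes a two-group model when one is meant.

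**Working it through.** **1. The plan's own figures.** The article gives no numerical figure for Aim 2. Its only power figures are for EPDS (Power and sample size). With detectable difference = (1.960 + 0.842) × SD × √((1+ρ)/2) × √(1/n₁ + 1/n₂), SD 6.24, n = 164 and 117:

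- ρ = 0.5, 0.4, 0.3 gives 1.83, 1.77, 1.71 (stated: 1.8, 1.8, 1.7).
- 123 and 88 after 25% dropout, ρ = 0.5, gives 2.11 (stated: 2.1).

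These reproduce. The present point does not depend on them.

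**2. Algebra.** Write the Aim 2 model with baseline covariates x as

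y_it = a + τ_t + b′x_i + u_i + e_it.

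Then y_it − y_i0 = (τ_t − τ_0) + (e_it − e_i0). The term b′x_i cancels. With complete data the estimated time effects are mean within-person differences, so adding x cannot move them.

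**3. Simulation of the model as written.** From the article: 164 recipients, three waves, mean 10.45, 25% dropout. Assumed, not in the article: SES effect −1.5 per SD, 0.5 per unit of parity, 1.5 for a health condition; intercept and residual SD 4.4 each (√(4.4² + 4.4²) = 6.22, close to the stated 6.24, correlation 0.5); a 1.5-point fall after baseline, all of it secular and none due to cash. There were 60 replicates per scenario.

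| Scenario | Time effect, unadjusted | Adjusted for baseline SES, parity, health condition | Mean shift | Largest shift |
|---|---|---|---|---|
| Complete data | −1.426 | −1.426 | 0 | 1e-13 |
| 25% dropout at random | −1.513 | −1.503 | 0.009 | 0.10 |
| About 25% dropout depending on SES | −1.698 | −1.529 | 0.169 | 0.35 |

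The standard error with complete data was 0.484 before and after adjustment. The simulation error of the mean is about 0.484/√60 = 0.06, so −1.426 agrees with −1.5. In the last row, adjustment removes attrition bias (−1.70 to −1.53, true value −1.5). In every row the full secular fall remains and would be read as change under cash.

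**4. The same covariate in a two-group model.** Inputs: 164 v 117, group and time-by-group terms, true cash effect 0, the same 1.5-point secular fall in both groups, and an assumed SES imbalance of 0.3 SD. Expected unadjusted bias is −1.5 × 0.3 = −0.45. Simulated average post-baseline difference: −0.43 unadjusted, 0.07 with baseline SES. Here the check does its job, and the secular fall is shared by both groups and drops out. The time-by-group term stayed at 0.104 with and without SES, because it is a contrast of within-person changes.

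**The case against.** The strongest objection is that the sentence after the check promises a between-group difference. If that sentence governs and a group term is fitted, baseline adjustment is informative, as step 4 shows. This stands as a limit: the point applies to the model that is written. It does not remove the point, because the written model and the promised quantity cannot both be right.

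Second, exact cancellation needs a linear model and complete data. That stands. The article projects 25% dropout, and several Aim 2 measures are not continuous three-wave scores: perceived stress in three groups, financial wellbeing in quartiles, a two-question food screener, and prenatal care adequacy taken once from the birth certificate. Non-linear models were not simulated. Adjustment can help against attrition in a time-only model, but that is a different purpose from checking confounding.

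Two stronger readings are tempting.

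- A reader might infer that the check would adjust away the cash effect, since SES is what cash changes and "Ability to meet basic needs will be measured through three domains: financial, food, and housing insecurity". With SES updated at each wave and cash assumed to act wholly through it, a simulated effect went from −1.51 to −0.02. But this result restates its own assumption, and neither Aim 2 nor Aim 3 says that covariates will be updated after baseline. Their timing is ordinary analysis-plan detail. The same holds for parity updated at birth: the mean moved only from −1.51 to −1.44, while the standard error rose from 0.49 to 0.64.
- A reader might infer that Aim 3's check has the same fault. It does not, because that model has group and time-by-group terms.

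**Conclusion.** The concern holds for Aim 2 as written. In a recipients-only model with time and a random intercept, adjusting for baseline SES, gravidity, parity and health conditions cannot show whether a change comes from the cash or from the pregnancy-to-postpartum transition. For a linear outcome with complete data the shift is zero; with about 25% SES-dependent dropout it averaged 0.17 and reflected attrition. The zero shift is algebraic. The other sizes rest on the assumed covariate effects, variances and dropout model.

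The underlying fault is that Aim 2's model lacks the group terms needed for the between-group difference it promises. The article does not support the wider claims that the check fails in any model, that it would remove the cash effect, or that Aim 3 is in error.

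**What to change.** Reconcile the Aim 2 text. For repeated survey outcomes, use the Aim 3 form: fixed effects for time, group and time-by-group, with participant random intercepts, in the 164 cash + care and 117 care-only participants already enrolled. Suggested wording: *The covariate sensitivity analysis will be applied to the average post-baseline difference between groups and will use values recorded at the baseline survey. Adjustment of a recipients-only model of change over time will not be presented as a check on confounding.* Prenatal care adequacy is recorded once and needs a single-time two-group comparison instead.

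Naming baseline-survey values is a wording safeguard. Covariate-by-time interactions are optional, and they have no meaning for Aim 3's single-time logistic models of birth outcomes.

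No new data are needed. The cost is a few model terms and possibly a wider interval. On the EPDS scale with SD 6.24 and ρ = 0.5, the standard error of the mean of two follow-ups minus baseline in recipients is √(6.24² × 0.5 × 1.5/164) = 0.42. For the between-group post-baseline difference it is 6.24 × √0.75 × √(1/164 + 1/117) = 0.65. That loss of precision is worth accepting, because the narrower interval belongs to a contrast that does not isolate the cash.

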#### Outcomes

Low birth weight will be extracted from the birth record and defined as an absolute weight of <2,500 g regardless of gestational age (27). Preterm birth will be extracted from the birth record and defined as birth prior to 37 weeks gestation (27).

Depression will be assessed using the Edinburgh Postnatal Depression Scale (EPDS), a measure validated for use during and up to 24 months after pregnancy (28–31). The scale consists of 10 items scored on a 4-point Likert scale which ask about common depressive symptoms experienced in the prior week. We will characterize this primary outcome using a continuous score because subclinical symptoms can impact functioning (32, 33). Additionally, we will characterize probable depression (yes vs. no) using a cut-off score of ≥11 (34). Anxiety will be assessed using the Generalized Anxiety Disorder scale-7 (GAD-7) score (continuous) which is a reliable and validated measure for use during and after pregnancy. The GAD-7 consists of 7 items scored on a 4-point Likert scale which ask about common anxiety symptoms in the prior 2 weeks (range 0–21).

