#### Power and sample size

This study is powered on detecting a difference in EPDS depression score between the cash + care vs. care groups during the 6- to 12-month postpartum period (Aim 3). Preliminary data from eligible participants suggest a mean Edinburgh Postnatal Depression Scale (EPDS) score of 10.45. Table 1 presents the estimated minimum detectable differences in depression scores between the two groups given a total of 281 participants with 164 in the cash + care group and 117 in the care-only group. We assumed two observations per participant (6- and 12-months postpartum) after initiation of the cash + care or care only interventions, a standard deviation of 6.24 (based on preliminary data), a significance level (two-sided alpha) of 0.05, and a within-participant correlation ranging from 0.3 to 0.5. For example, we achieve 80% power to detect a 1.8 point mean difference in EPDS score between the care-only group and the cash + care group, given a within-participant correlation of 0.5. A clinically meaningful difference on the EPDS scale is defined as a change of 4 points for improvement (43). Given our current sample size, we will have sufficient power to detect these clinically significant differences. Even with a projected 25% dropout rate for both groups (e.g., 123 in the cash + care group and 88 in the care-only group), we will still be able to detect a minimum difference of 2.1. All power calculations were carried out using PASS (44).

**Table 1 tab1:** Estimated minimum detectable differences in depression scores.

Within-participant correlation	Mean difference
0.5	1.8
0.4	1.8
0.3	1.7

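### The random-intercept model for the primary EPDS analysis assumes equal variances and correlations across three unevenly spaced waves, so its confidence interval may be miscalibrated in either direction

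*Protocol article*

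**What the plan says.** The Outcomes section of the protocol article says of the EPDS: "We will characterize this primary outcome using a continuous score". Under Quantitative data analysis, Aim 3, the primary model has "fixed effects for time (baseline, 6 months postpartum and 12 months postpartum), group", then "the interaction between time and group and random participant-level intercepts". The target follows: "we will estimate and report the average difference in depression score between groups over follow-up with 95% confidence intervals". The same paragraph extends the approach to the anxiety score.

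Aim 2 uses "mixed effects regression models with a fixed effect for time (categorical) and random participant-level intercepts". Neither aim mentions a residual covariance structure, a random slope or robust standard errors.

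On timing: "Quantitative data collection takes place at enrollment (12–24 weeks gestation) and at 6 and 12 months postpartum". The Power and sample size section uses only the two postpartum observations, with a single within-participant correlation between 0.3 and 0.5 and a standard deviation of 6.24, "given a total of 281 participants with 164 in the cash + care group and 117 in the care-only group".

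The preliminary-analysis paragraph promises that model assumptions will be checked. The only remedy it names is transforming variables.

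**The concern.** A random intercept with independent, constant-variance residuals is compound symmetry: one variance at every wave and one correlation for every pair of waves. The design gives reason to doubt this. Assuming delivery near 40 weeks, the baseline survey falls 16-28 weeks before birth. The gaps are then about 10-12.5 months (baseline to 6 months), 6 months (6 to 12 months) and 16-18.5 months (baseline to 12 months). The closest pair is also the pair in which both surveys are postpartum. If correlation falls with distance in time, the 6-12 month correlation is the largest of the three.

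The true variance of the postpartum average depends on the 6-12 month correlation alone. Once baseline is a response, the fitted model replaces that correlation with the average of all three. At stake is the calibration of the primary confidence interval and of any test based on it.

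**Working it through.** **Inputs from the article.** SD 6.24; 164 and 117 participants; two-sided alpha 0.05; 80% power; postpartum correlation 0.3-0.5; 123 and 88 after 25% dropout.

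**Step 1: reproduce the stated detectable differences.** The formula is MDD = (1.960 + 0.842) × 6.24 × √[((1+ρ)/2) × (1/n₁ + 1/n₂)]. With 164 and 117, √(1/164 + 1/117) = 0.1210.
- ρ = 0.5: 1.83 (stated 1.8)
- ρ = 0.4: 1.77 (stated 1.8)
- ρ = 0.3: 1.71 (stated 1.7)
- 123 and 88, ρ = 0.5: 2.11 (stated 2.1)

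The figures reproduce. They use only two waves, so there is one correlation and nothing to average, and the present point leaves them untouched.

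**Step 2: model and true standard error for the postpartum average.** With complete data, equal variances and a saturated time-by-group mean, the random-intercept fit pools the three correlations to their mean, r̄. The model variance factor is (1 + r̄)/2 and the true factor is (1 + r₆,₁₂)/2. The SE ratio is R = √(model/true), and type I error = 2 × [1 − Φ(1.96 R)].

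The correlations below are assumed, in the order baseline-6m / baseline-12m / 6m-12m.

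| Correlations | r̄ | Model factor | True factor | R | Type I error |
|---|---|---|---|---|---|
| 0.5/0.5/0.5 | 0.500 | 0.750 | 0.750 | 1.000 | 5.0% |
| 0.4/0.35/0.5 | 0.417 | 0.708 | 0.750 | 0.972 | 5.7% |
| 0.4/0.3/0.5 | 0.400 | 0.700 | 0.750 | 0.966 | 5.8% |
| 0.3/0.3/0.5 | 0.367 | 0.683 | 0.750 | 0.955 | 6.1% |
| 0.4/0.3/0.6 | 0.433 | 0.717 | 0.800 | 0.946 | 6.4% |
| 0.28/0.14/0.5 | 0.307 | 0.653 | 0.750 | 0.933 | 6.7% |
| 0.5/0.5/0.3 | 0.433 | 0.717 | 0.650 | 1.050 | 4.0% |

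The sixth row is exponential decay over gaps of 11, 17 and 6 months with 0.5 at 6 months: 0.5^(11/6) = 0.28 and 0.5^(17/6) = 0.14. In EPDS points, the 0.4/0.3/0.5 row is a reported SE of 0.632 against a true 0.654.

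**Step 3: dropout.** REML simulations (1,000 replicates per pattern, starting from 164 and 117, 25% lost by 12 months) for patterns with the 6-12 month correlation highest gave SEs about 3-7% too small and coverage of 92.6-94.0%. The Monte Carlo error on coverage is about √(0.94 × 0.06/1000) = 0.75 percentage points, so this supports the closed form without refining it.

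**Step 4: unequal variances.** Take 0.4/0.3/0.5 with baseline SD 6.24.
- Postpartum SD 7 (assumed). The mean variance is (38.94 + 49 + 49)/3 = 45.65 and the mean covariance (17.47 + 13.10 + 24.50)/3 = 18.36. Model (45.65 + 18.36)/2 = 32.00, true (49 + 24.5)/2 = 36.75, R = 0.933, type I error 6.7%.
- Postpartum SD 5.5 (assumed). The same steps give model 23.10, true 22.69, R = 1.009, type I error 4.8%.

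**Step 5: a single time point.** At equal variances the 12-month difference has R = 1.000, so there is no effect.

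**The case against.** The strongest reply is that a condensed article does not say the intercept is the only covariance term. Residual structure and the type of standard error commonly sit in an analysis plan, which is not shown, and the article promises assumption checks. This stands in part: the point applies to the model as published, and a fuller plan may already settle it. But the article does choose a dependence structure, and transformation does not cure unequal correlations.

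The second reply is that direction and size are not known. This stands in full. The article gives no pairwise correlations and no wave-specific variances. If all three correlations lie between 0.3 and 0.5, the largest type I error in Step 2 is 6.1%, and the reverse ordering makes the interval conservative.

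Three stronger readings are tempting and are not supported:
- **That the primary interval is too narrow.** This needs the 6-12 month correlation to exceed the average of the three, with no offsetting difference in variances. The documents establish neither.
- **That the type I error reaches 8.5%.** That figure is for change from baseline. With 0.4/0.3/0.6, the model factor is 1.5 × (1 − 0.433) = 0.85 and the true factor is 1 + 0.80 − 0.70 = 1.10, so R = 0.879. Aim 3 describes the average between-group difference over follow-up, and the power section concerns the 6- to 12-month postpartum period. Neither specifies change from baseline.
- **That every Aim 2 outcome is affected.** Perceived stress is to be grouped in three classes and financial wellbeing in quartiles. Adequacy of prenatal care comes once from the birth certificate. The attachment scale asks about the baby, so presumably has only postpartum waves. The arithmetic covers continuous outcomes measured at all three waves.

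**Conclusion.** The point holds in a limited form. As written, the primary model ties three unevenly spaced waves to one variance and one correlation, and the interval for the average postpartum difference inherits any misfit. At equal variances, if the 6-12 month correlation is the highest, the SE is about 3-7% too small and the type I error about 5.7-6.7%. If it is the lowest, as in 0.5/0.5/0.3, the type I error is about 4.0%. With equal correlations there is no error.

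These sizes rest on assumed correlations, and wave-to-wave differences in variance could move them either way. No stated figure is wrong and nothing in the article is contradicted. The case for change is that the effect bears on the primary interval and can be removed almost for free.

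**What to change.** For EPDS, GAD-7 and any other continuous outcome measured at all three waves, keep the fixed effects as planned and state one of the following:
- an unstructured 3×3 residual covariance in place of the random intercept; or
- the random intercept with participant-clustered robust standard errors.

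Either protects the standard error whichever way the correlations or variances fall. With dropout, the unstructured model has the further advantage that its point estimates do not lean on compound symmetry; robust standard errors leave the point estimates as they are.

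The unstructured matrix has six covariance parameters against two for the random-intercept model. That is four more, with about 211 (123 + 88) to 281 participants. The change is one option in the model statement and should be fixed before outcome data are examined by group.
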